## Abstract

**Background:**

Providing appropriate support and care for end-of-life patients and their relatives is a major concern and a daily responsibility for intensivists. Bereaved relatives of non-surviving patients in intensive care units (ICUs) often suffer from prolonged grief, posttraumatic stress disorder, anxiety, and depression. A physician-driven intervention, consisting of three meetings with the family, might reduce the post-ICU burden of bereaved family members 6 month after death. The patient’s nurse is actively involved at each step. We hypothesize that this strategy will improve communication in the end-of-life setting and thus, should reduce the post-ICU burden for family members, specifically the development of prolonged grief 6 months after the death.

**Methods/design:**

The COSMIC-EOL trial is a prospective, multicenter, cluster randomized controlled trial in which centers are allocated to two parallel arms: (1) intervention centers where relatives benefit from three-step physician-driven support during the dying and death process and (2) control centers where, during the dying and death process, relatives receive the standard of care practice. Each of the 36 participating centers will include 25 relatives of patients with a length of stay ≥2 days. Participating relatives will be followed up by phone at 1, 3, and 6 months after the patient’s death to complete questionnaires permitting evaluation of their post-ICU burden. The main outcome is prolonged grief measured 6 months after the death using the PG-13. Other outcomes include evaluation of quality of dying, quality of communication, anxiety, depression, and post-traumatic stress. The estimated duration of the study is 36 months.

**Discussion:**

The results of the trial will provide information about the effectiveness of physician-driven support for relatives of patients dying in an ICU. The study is expected to demonstrate a decrease in the ICU burden for bereaved relatives who benefitted from this intervention.

**Trial Registration:**

ClinicalTrials.gov, NCT02955992. Registered on November 3rd 2016.

**Electronic supplementary material:**

The online version of this article (10.1186/s13063-018-3084-7) contains supplementary material, which is available to authorized users.

## Background

### End-of-life and family burden

Providing appropriate support and care for end-of-life (EOL) patients and their relatives is a major concern for intensivists and, with a mortality rate of 20%, it has become a daily responsibility. Among those deaths, over 60% follow a decision to withhold or withdraw treatment [1]. In these situations, physicians, nurses, and relatives must work together towards the most consensual decision. In an intensive care unit (ICU), relatives are no longer simple visitors: they play active roles both at the patient’s bedside and with the team, thus creating a complex and unprecedented interaction. Caring for relatives is now considered one of the responsibilities of an ICU caregiver [2].

In this context, patients’ relatives feel vulnerable and, in the months that follow the death, they are at high risk of presenting symptoms that negatively affect their quality of life, such as anxiety, depression, posttraumatic stress disorder (PTSD) symptoms [3, 4], and complicated grief. In a recent study [1], 52% of relatives presented complicated grief symptoms 6 months after the patient’s death, a fivefold higher frequency compared with the general population [5, 6]. The post-ICU burden is very high in bereaved relatives and requires specific attention.

### The importance of communication

Many studies have shown that communication with caregivers is one of the most highly valued aspects of care [7–9]. It impacts family members’ experience during the patient’s stay and after the patient’s death. Communication perceived as inconsistent, unsatisfactory, or uncomforting is associated with a higher risk of presenting with post-ICU burden [10]. The risk of presenting with PTSD-related symptoms increases when bereaved relatives feel that information is incomplete [4]. Discordance between family members’ preferences for decision-making and their actual decision-making roles is associated with a higher risk of presenting with PTSD symptoms [11]. Bereaved relatives reporting poor quality of communication are more at risk of developing complicated grief and PTSD-related symptoms [1].

Communication is an essential component of family support and can be both verbal and nonverbal. The quality of information is crucial in the ICU context, but physicians’ and nurses’ attitudes and their ability to express empathy, comfort, and reassurance also significantly affect relatives’ experience. Indeed, relatives who experienced the physician’s attitude as non-comforting are at higher risk of developing a post-ICU burden or complicated grief [12]. Effective listening is an important aspect of communication. During family meetings, ICU physicians often miss opportunities to listen and respond to the needs of the next of kin [13]. In a study by Selph and colleagues, there was a significant positive correlation between the number of empathic statements made during family conferences and the degree of family satisfaction with communication [14].

### Support for family members

Support for family members is a core function of palliative care. The need to improve communication during the EOL process in the ICU context is recommended in palliative care and family-centered care guidelines [15–17]. Effective communication, empathetic attitudes, and personalized interactions with a patient’s family can improve the bereaved family's long-term psychological outcomes [18]. Rather than being considered as passive visitors, relatives are encouraged to become active partners in EOL decision-making and care, creating opportunities for empowerment.

Communication is important throughout the patient’s ICU stay, from their admission to their death. Moreoever, communication surrounding EOL is crucial. During this period, relatives undergo considerable distress. Their experience resembles a vortex [19]: a downward spiral of prognoses, difficult decisions, feelings of inadequacy, difficulties in saying good-bye, ending with the loss of the loved one despite the technical efforts of the ICU. Communication may be the most important factor in EOL care in ICUs [20].

### Three communication opportunities

Based on our experience, in the EOL process, there are three critical communication opportunities with relatives of patients dying after a decision to withhold or withdraw life-sustaining treatment. This randomized trial intends to target each of these three stages specifically.

First, there should be an interview to prepare the relatives for the patient’s imminent death and to elicit their understanding of the situation [21]. The death of a loved one can create feelings such as fear, relief, panic, or disbelief, and relatives need opportunities to express their feelings and emotions and to discuss the organization of the dying process (spiritual beliefs and needs, possible involvement in the patient’s care, and their presence at the time of death) [22–25]. Attentive listening is a key component of EOL interviews. In this study, this step is an extension of the VALUE approach [21, 26], updated by findings from recent research [1, 27].

The second opportunity occurs during the dying and death process. Dying after implementing a decision to withhold or withdraw treatment can take time, time during which relatives are often at the patient’s bedside. For families, being present during the dying period is a complex experience. Relatives seek intimacy but also need explanations and reassurance [8]. A room visit from the physician and from the nurse gives opportunities for families to express their feelings and ask specific questions concerning the following [15]: spiritual beliefs, tenets of palliative care, the expected time of death, and their possible role in the patient’s care [28]. Some relatives need guidance as to what is the best way to support the person who is dying. Caregivers can encourage the relative to touch the patient, to close the curtains, or to do whatever may be appropriate in that specific situation.

The third opportunity is a post-death encounter [29]. In a qualitative study by Nelson and colleagues, relatives who experienced clinicians as supportive during the ICU stay nonetheless perceived an abrupt and distressing shift at the time of death [8]. Many relatives often have questions regarding the patient’s stay, the patient’s illness, and the patient’s death. No answers to these questions can hinder the grieving process. Furthermore, during the patient’s stay, relatives develop relationships with the staff, physicians, and nurses, and need an opportunity to say good-bye to them. Closure with the team that cared for the patient permits grieving [30].

ICU caregivers have a great deal of responsibility in facilitating relatives’ involvement and in limiting their stress and difficulties. Results from various studies show that relatives’ satisfaction depends on the attitude of the caregivers as well as on good communication, good listening, and good information [31]. Communication at the EOL is a process that cannot be reduced to one interview. Providing multiple opportunities for relatives to ask questions, to express emotions, and to find comfort and support is an important aspect of palliative care.

In this randomized controlled trial, we will study efforts to integrate palliative care communication in intensive care more effectively and efficiently and will document any improvement using valid and responsive outcome measures.

### Meeting palliative needs in the ICU

There have been several studies suggesting that interventions to improve communication in the ICU could improve EOL care. To date, only very few intervention studies have examined patient- or family-centered outcomes. The first [21] focused on family conferences before the patient’s death. This positive randomized trial demonstrated that a proactive family conference and a bereavement pamphlet for relatives reduce post-traumatic stress symptoms 3 months after the death. However, 45% of relatives still presented with PTSD-related symptoms in the intervention group (compared to 69% in the control group), leaving space for more improvement.

The second [32] focused on clinician training. This negative cluster-randomized trial targeted five components of clinical care: clinician education, local champions, academic detailing, clinician feedback of quality data, and system supports. It showed no improvement in quality of dying and no change in ICU length of stay prior to death or time from ICU admission to withdrawal of life-sustaining measures. This shows that improving ICU EOL care requires interventions with more direct contact with patients and family, as in the previous study.

A third more recent study [33] showed that family informational and emotional support meetings led by palliative care clinicians does not improve family anxiety and depression; it may even increase PTSD symptoms. These findings do not support routine or mandatory palliative care-led discussion of the goals of care for all families of patients with a chronic critical illness.

For the first time, we propose a study with a direct ICU physician-driven intervention during the dying and death period, the most crucial time for family members. We designed a three-step physician-driven support strategy that consists of three meetings with the relative: one before, one during, and one after the patient’s death. The patient’s nurse is actively involved at each step.

### Hypothesis

We hypothesize that this strategy will improve communication in the EOL setting and thus, should reduce the post-ICU burden for family members, specifically the development of prolonged grief 6 months after the death.

## Methods/design

The COSMIC-EOL trial (Communication Strategies and Measures in Intensive Care at End of Life) is a prospective, multicenter, cluster randomized controlled trial. Centers are allocated to two parallel arms: (1) intervention centers where relatives benefit from three-step physician-driven support during the dying and death process and (2) control centers where, during the dying and death process, relatives receive the standard of care practice. This design was used to reduce the effect of intervention contamination, given that it involves training and education of health professionals to improve patient care.

### Objectives

This study aims to assess whether a three-step physician-driven support strategy during the dying and death process in the ICU can reduce patients’ relatives’ symptoms of prolonged grief 6 months after the patient’s death.

Secondary objectives are to evaluate in both groups of relatives: their experience of dying and death in the ICU; their satisfaction with EOL communication (specifically their rapport with the physician); and the impact on them of the three-step physician-driven support during the dying and death process on symptoms of anxiety, depression, and PTSD 1, 3, and 6 months after the death.

### Study setting

The study will take place at 36 ICUs in France (Additional file 1).

### Eligibility criteria

ICUs with ≥8 beds, a ratio of 1/2.5 nurses per patient, and 24 × 7 medical coverage were eligible. Participating centers were selected from (1) the Famiréa network, based on previous and repeated participation in Famiréa studies and (2) a list of centers that had never participated in Famiréa studies. Famiréa is a French research group that aims to study family members’ experience both during and after the patient’s ICU stay to improve practices, specifically communication skills and EOL care. Since its creation 20 years ago, it has promoted research into family-centered care in a network of ICUs that strive to put into practice the findings of published studies.

The study population consists of bereaved family members after the death of an adult patient in an ICU who fulfil all the inclusion criteria and none of the exclusion criteria.

Relatives of patients who meet the following criteria are included: patient >18 years who died in an ICU after a decision to withhold or withdraw treatment and ICU length of stay ≥2 days. To be included, relatives must be available to give consent to participate in the study. Relatives who do not understand, read, or speak French or who refuse to participate are excluded, as well as relatives of organ donor patients (as these relatives benefit from specific support and adapted communication by the transplant coordination teams).

As in previous Famiréa studies [1, 4, 21], only one family member is included. This family representative is the designated health-care proxy. In their absence, this is the family member most involved in the relationship with the ICU team, or by default is the spouse (or partner). In their absence, it is the parents or children of the patient, then another member of the family.

### Methodology

This protocol follows the Standard Protocol Items: recommendations for interventional trials (SPIRIT) checklist (Additional file 2). The SPIRIT recommended schematic diagram detailing the schedule of enrolment, interventions and assessments is provided as Fig. 1.

**Fig. 1 Fig1:**
[figure not shown]
SPIRIT figure. HADS Hospital Anxiety and Depression Scale, ICU intensive care unit, IES-R Impact of Event Scale, Revised, MISS-21 Medical Interview Satisfaction Scale, PG-13 Prolonged Grief 13-item questionnaire, QODD-1 Quality of Dying and Death 1-item questionnaire

#### Randomization

Participating centers are assigned by simple random allocation to one of the two groups in a 1:1 ratio. Each subject is treated according to the strategy allocated to the center (Fig. 2). The randomization between the two parallel groups of centers was centrally generated by a statistician not involved in the study using permuted and balanced blocks of non-released size. Randomization is stratified using recruitment period, and also on centers’ previous participation in Famiréa studies (experienced vs. new centers).

**Fig. 2 Fig2:**
[figure not shown]
Study design

Relatives are included after the decision to withhold or withdraw treatment has been made using a signed consent form approved by the institutional review board. Relatives who consent to participate are contacted by phone three times: 1, 3, and 6 months after the patient’s death. All telephone calls are done by trained sociologists and psychologists from the Famiréa group. Telephone interviewers are blinded (control vs. intervention). The estimated duration of each call 1, 3, and 6 months after the patient’s death is 40 min, 30 min, and 30 min, respectively.

#### Study arms

Intervention pertains to the cluster and individual participant level.

In the control group, the bereaved relatives receive usual care during the dying and death process. In the intervention group, the bereaved relatives receive the three-step physician-driven support during the dying and death process. Relatives attending control or intervention centers are followed up by the Famiréa research group using telephone interviews 1, 3, and 6 months after the death to complete the questionnaires. This method has been validated in numerous follow-up studies of bereaved relatives [1, 4, 21].

The control centers manage the EOL process and communication with relatives using their standard of care. In these centers, EOL care is described for each patient in the patient’s characteristics form, which is used to record those who spontaneously benefited from a family conference, from a room visit during the dying and death process, or from a post-death meeting.

The intervention centers implement the three-step physician-driven support strategy. In these centers, prior to patient recruitment, the three-step communication strategy is presented to caregivers using video support. The team (physicians and nurses) then attend interactive educational meetings to set the importance of EOL communication. These meetings are led by members of the Famiréa research group and will cover themes such as family experience in the ICU and their experience of EOL, the impact of the ICU experience on bereaved relatives, communication in the EOL context, what families recall 1 year after the patient’s death, what caregivers can do to improve families’ experience and alleviate their burden, etc. All caregivers receive a leaflet about the importance of EOL communication. This lists the key elements (the impact of communication on a family’s post-ICU burden) and recommendations regarding verbal and nonverbal communication. As recommended in the literature on implementing guidelines [34–36], a local champion (or opinion leader) is designated by each team to help implement the strategy. An implementation phase of one month is required for the team to test and to get accustomed to the intervention as well as to discuss difficulties with the principal investigator.

Centers implement the three-step physician-driven support for a family after a decision to withhold or withdraw life-sustaining therapies, as shown in Table 1. The intervention is accompanied by a fidelity checklist to control adherence to the protocol.

**Table 1 Tab1:** Study intervention: a three-step communication strategy

Three-step strategy	Preparation for death The physician and the nurse meet the relative to:	During the dying and death process:	After the patient’s death The physician and the nurse meet the relative to:
Themes	▪ Prepare the relative for the patient’s imminent death ▪ Provide an opportunity for relatives to ask questions ▪ Provide an opportunity for relatives to express their feelings and emotions ▪ Encourage relatives to talk to the patient and say good-bye ▪ Discuss being present at the time of death ▪ Discuss possible involvement in the patient’s physical care ▪ Discuss spiritual beliefs and needs	▪ The physician enters the patient’s room at least once to check whether the relatives have any questions or apprehensions and to check their comprehension of what is happening ▪ The nurse enters the patient’s room at least once to check the relatives’ comfort and needs, and whether they have any questions	▪ Express their condolences ▪ Elicit and answer questions about the patient’s death ▪ Provide an opportunity for relatives to express their feelings ▪ Offer them the option of contacting the team during their bereavement
Mnemonic	PRECISE: ▪ Prepare ▪ Relatives for the patient’s death ▪ Elicit questions and emotions ▪ Communication about presence at time of death and ▪ Involvement in care ▪ Spiritual needs ▪ Encourage relatives to say good-bye to the patient	RAAP: ▪ Reassure relatives regarding their spiritual beliefs, the tenets of palliative care, the expected time of death, and their role in the patient’s care ▪ Answer relatives’ questions ▪ Attentive listening ▪ Propose emotional support	CIAO: ▪ Condolences: express condolences ▪ Instigate questions about the patient’s ICU stay and death ▪ Acknowledge emotions ▪ Option to contact the team during their bereavement

In two of the intervention centers, an outsider observer (a sociologist) will observe clinical practices and meetings with the family members at steps 1, 2, and 3. The aims are (1) to complete the checklists independently and compare them with those completed by caregivers and (2) to observe nonverbal communication (voice, touch, and distance), such as the synchronization between nonverbal communication and emotions and caregivers’ capacity to adapt to each emotional situation.

#### Qualitative interviews

To evaluate the communication strategy and also to provide an in-depth comprehension of relatives’ experience of EOL communication in both arms (control and intervention), semi-structured interviews are organized voluntarily with relatives. The interviews are led by sociologists with extensive experience of research with bereaved relatives. Themes include: their memories of EOL care, their communication with physicians (verbal, nonverbal, and empathy), their communication with nurses (verbal, nonverbal, and empathy), their communication with the dying patient, time of death, post-death communication, and interaction with the ICU team.

#### Outcomes

Outcomes are at the individual patient level. The primary outcome is the Prolonged Grief 13-item questionnaire (PG-13) [37], completed 6 months after the patient’s death. The PG-13 measures five criteria for prolonged grief disorder: event (bereavement); separation distress; duration (i.e., >6 months since the bereavement); cognitive, emotional, and behavioral symptoms; and social or occupational impairment. The score range is 11–55 and a score of 36 or more is a clinical indicator of prolonged grief disorder. In addition, all five criteria must be met.

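### The primary PG-13 call is set at 6 months, but the five-criteria definition of prolonged grief disorder needs more than 6 months: a conflict if that definition is the primary case rule

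*Protocol article*

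**What the plan says.** Four statements bear on the point.

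- **Instrument and time.** Under Outcomes: "The primary outcome is the Prolonged Grief 13-item questionnaire (PG-13"), "completed 6 months after the patient’s death".
- **Duration criterion.** The same paragraph names five criteria for prolonged grief disorder. One is "duration (i.e., >6 months since the bereavement"), a strict inequality.
- **Case rule.** After the 11–55 score range, the paragraph says that "a score of 36 or more is a clinical indicator of prolonged grief disorder", and then: "In addition, all five criteria must be met".
- **Call schedule.** The text under Fig. 2 says that consenting relatives are "contacted by phone three times: 1, 3, and 6 months after the patient’s death". The abstract and the Study arms section give the same 6-month point.

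The Statistical analysis section plans the sample size on a proportion with complicated grief symptoms at 6 months (50% against 35%). It also says that scores will be analysed both as recorded and, where they exist, by established cutoffs. The Objectives section speaks of symptoms of prolonged grief.

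**The concern.** The nominal assessment time lies on the excluded side of the duration criterion. Exactly 6 months is not more than 6 months. Under a rule that requires every criterion, a relative reached on the due date or shortly before it cannot be a case, even with the highest possible score. Case status would then depend partly on the date of the telephone call.

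What is at stake is the binary grief endpoint on which the trial is powered. Relatives who are negative only because of the calendar lower the observed rate in each arm and shrink the absolute difference, so power falls. The estimated prevalence of prolonged grief disorder would also be too low.

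**Working it through.** **Step 1: the logic.** The inputs are the assessment time, the duration criterion and the all-criteria rule, all from Outcomes. Let t be the time from death to the call.

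- If t ≤ 6 months, the duration criterion fails.
- If one criterion fails, the all-criteria rule fails.
- So the five-criteria classification is negative for every t ≤ 6 months, whatever the score.
- If t > 6 months, even by one day, the criterion is met and nothing is lost.
- The raw score and the bare cutoff of 36 do not contain t and are unaffected.

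**Step 2: reproduce the planned size.** Inputs from Statistical analysis: p1 = 0.50, p2 = 0.35, two-sided α = 0.05, power 90%. With the pooled-variance formula and no continuity correction, mean rate p̄ = 0.425:

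n = [1.960 × √(2p̄(1 − p̄)) + 1.282 × √(p1(1 − p1) + p2(1 − p2))]² / (p1 − p2)²

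= [1.960 × √0.48875 + 1.282 × √0.4775]² / 0.15²

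= (1.370 + 0.886)² / 0.0225 ≈ 226.2, rounded up to 227 per arm, 454 in total.

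This matches the article. Power at 227 per arm is 90.1%.

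**Step 3: the size of the effect.** Let f be the share of assessed relatives called at or before 6 full months. The article gives no call dates, so f is an assumption with range 0–100%. Take f as equal in the two arms and unrelated to true grief status. The observed rates become q1 = 0.50(1 − f) and q2 = 0.35(1 − f). With q̄ their mean and n = 227:

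power = Φ{ [(q1 − q2)√n − 1.960 × √(2q̄(1 − q̄))] / √(q1(1 − q1) + q2(1 − q2)) }

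For f = 10%: q1 − q2 = 0.135, 2q̄(1 − q̄) = 0.4724, and the last term is √0.4633. The bracket gives 1.009, so power = Φ(1.009) = 84%.

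| f (assumed) | Control | Intervention | Difference | Power |
|---|---|---|---|---|
| 0% | 50.0% | 35.0% | 15.0 points | 90% |
| 5% | 47.5% | 33.3% | 14.3 points | 87% |
| 10% | 45.0% | 31.5% | 13.5 points | 84% |
| 25% | 37.5% | 26.3% | 11.3 points | 73% |
| 50% | 25.0% | 17.5% | 7.5 points | 50% |
| 100% | 0% | 0% | none | no comparison |

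The table uses 227 effective relatives per arm, the article's figure before its inflation for clustering and loss to follow-up. That isolates the effect of call timing. Whether those inflation steps are right is a separate question and plays no part here.

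**The case against.** **The endpoint may not be the five-criteria diagnosis.** The article names the PG-13 questionnaire as primary outcome, frames the aim as reducing symptoms, and lists analyses by score and by cutoff. The all-criteria sentence can be read as a description of how the instrument defines the disorder. This stands in part. It means that the harm is conditional and that one cannot say outright that relatives will be forced negative. It does not remove the point, because the all-criteria rule follows directly on the cutoff and nothing says that it is left out of the primary comparison.

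**A call window is a detail that an article leaves to the full protocol.** It is true that an unstated window is no fault in itself, and nothing in the article says that calls are made early. But the conflict lies between statements that the article does make: a strict inequality, an all-criteria rule and a time point that fails the inequality. A window centred on 6 months would not cure it.

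**The size is assumed.** This stands in full. At f = 5% the loss is only about 3 points of power, and if every call falls after 6 months there is none.

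**A reader might also infer bias between the arms.** If call timing differed by arm, forced negatives could create a false difference. The documents do not support that reading: both arms have one call schedule, the telephone interviewers are blinded, and randomization is stratified by recruitment period. The expected effect is similar dilution in both arms.

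**Conclusion.** The conflict in the text is real: the primary assessment time and the duration criterion cannot both be applied literally. Its consequence is conditional. If the five-criteria classification is the primary case definition, any relative called at or before 6 full months is negative regardless of symptoms. If the primary comparison uses the score, or the cutoff of 36 alone, it is untouched.

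The possible loss ranges from nothing, when all calls fall after 6 months, to an endpoint without events, when none do. The intermediate figures in the table rest on an assumed f that is common to both arms and unrelated to true grief status. They show how sensitive power is to call timing and do not predict what will happen in this trial.

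**What to change.** Reconcile the assessment time with the case definition in the Outcomes section. Either of two changes is enough:

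1. Open the primary call window only after 6 completed months since the death, in both arms, and record the days since death at each call.
2. State that the primary endpoint is the PG-13 score, or the cutoff of 36, without the duration criterion.

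Either takes a sentence or so. Under the first, the last calls may move by a few weeks, and days since death becomes one more recorded item. The second leaves the schedule alone, but the endpoint should then be described as a score or a score above the cutoff, since the article's own definition of prolonged grief disorder asks for more than that.
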